### Data collection

2.5.

Participant characteristics: Participants’ sex, age, educational level, occupation, stroke history, comorbidities, MFAC and MoCA scores will be extracted from the participants’ clinical records.Researchers defined acceptability a priori by four key domains for developing the program and performing a subsequent randomized controlled trial. These key domains include enrollment (number of stroke survivors that participate in the program), retention (number of classes attended and percentage of enrolled participants who completed final program assessments), and satisfaction (assessed with a survey and semi-structured exit interviews).

Safety via adverse events (number of events involving injury).

The study coordinator, who will not be involved in performing the intervention, will administer a customized post-intervention survey to assess participants’ acceptability of the intervention. The questionnaire will consist of Likert scale questions to evaluate the participants’ satisfaction. The interviews aim to gain insight into participants’ perspectives on the intervention’s acceptability and usefulness and identify exercise preferences, barriers, and facilitators that may influence the stroke survivor’s participation in the program.

The following outcome measures will be collected in the week before (T0) and the week after completing the training program (T1) by the following instruments:

Balance recovery will be measured using the Mini-Balance Evaluation Systems Test (mini-BESTest), a 14-item performance-based clinical scale subdivided into four subscales that measure different domains of balance, including anticipatory postural control, compensatory postural control, sensory orientation, and dynamic gait. Each item is scored from 0 to 2. “0” indicates the lowest level of function, and “2” is the highest level of function (31). Previous studies have shown that the Mini-Balance Evaluation Systems Test is reliable and valid for evaluating balance in stroke survivors (32).Functional mobility will be measured using the Timed Up and Go (TUG) Test. The Timed Up and Go Test is a reliable instrument to assess the subject’s mobility and functional balance as it requires the ability to transfer, walk, and change direction (33, 34). Participants will be seated in a chair with their backs supported. At the evaluator’s indication, participants must stand and walk 3 m in a straight line, turn back, return to the chair, and sit down as in the starting position. The test score is according to the participants’ time to complete the task. A task completed within 10 s indicates normal mobility; 11–20 s are within normal limits for frail or disabled adults with partial independence, and greater than 20 s is expected for people with an important deficit in mobility (33).

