## Abstract

Dance can be an innovative, well-accepted, and effective therapy for stroke survivors. The present protocol aims to assess the feasibility of adapted Portuguese folk dance as a post stroke rehabilitative activity. We will use a mixed-methods pilot study convenience sampling to recruit 16 stroke survivors with mild–moderate lower limb paresis from a rehabilitation center in Lisbon and Tagus Valley. In addition to usual care, participants will attend 3 days per week 1-h dance exercise for 8 weeks. The dance style used for this intervention will be an adaptation of the Portuguese folk dance. Assessment will be conducted before and immediately after the program intervention. Acceptability will be assessed by four key domains (enrollment, retention, satisfaction, and recommendation to others). Safety will be assessed based on the number and type of adverse events. Feasibility will be assessed based on balance performance and functional mobility. Quantitative data will be analyzed through descriptive statistics for sample characterization, followed by inferential statistics to evaluate differences in the balance recovery and functional mobility scores between the initial and final assessment. Qualitative data will be analyzed using an inductive process of content analysis. The Portuguese folk dance program has the potential to improve balance outcomes and functional mobility. Our results will help validate Portuguese folk dance as a tool for rehabilitation settings for stroke survivors. The potential of our program to enhance balance outcomes and functional mobility among stroke survivors bears implications for aging and public health initiatives. Positive results from this study could pave the way for integrating dance-based rehabilitative activities into standard stroke rehabilitation protocols, catering to older stroke survivors’ specific needs and preferences.

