### Sampling and recruitment

2.3.

The sampling method selection will be non-probabilistic by convenience. All stroke survivors that comply with the study criteria will be invited to join the program.

We aim to recruit 16 participants taking into account a dropout rate of 25% (29).

Inclusion criteria:

18 years old or above.Clinically diagnosed with ischemic or hemorrhagic stroke.Mild–moderate lower limb paresis with a modified functional ambulation classification (MFAC) of IV (assisted walker) or above.A Montreal Cognitive Assessment (MoCA) score > 20.Able to follow three-step directions.Able to tolerate a minimum of 45 min of exercise.Able to communicate with the investigator, to understand and comply with the study procedures.Show a preference for Portuguese folk dance Vira.Willing and able to provide written informed consent to participate and understand the right to withdraw their consent at any time without prejudice to future medical care.

Exclusion criteria:

Pre-existing neurological, cardiovascular orthopedic, or rheumatic disorder that could interfere with the execution of the proposed protocol;Severe hearing and visual impairment;Poor tolerance to a group setting or significant behavioral problems that would hinder the person from participating.

Two nurses from the rehabilitation center will be responsible for recruitment. In the first stage of recruitment, based on the data in the patient’s clinical file (diagnosis, stage of stroke, presence of hemiparesis, and clinical data), recruiters will identify stroke survivors as potentially eligible participants. In the second stage, a research team member will provide oral and written information regarding the study and recommend to each patient to take at least 24 h to reflect and discuss participation with their relatives/informal caregiver before deciding study to participate.

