### Intervention

2.4.

The intervention consists of an 8-week program (1-h group training, three times per week). This intervention will supplement the usual care, which consists of daily 45 min sessions of occupational and physical therapy.

The dance style used for this intervention will be an adaptation of the Portuguese folk dance Vira, performed in every region of Portugal. The translation of the name is “twist, turn.” It has a three-step rhythm and is similar to a waltz. First, participants dance in pairs, front-to-front, holding arms in the air without holding hands, forming a circle that moves counterclockwise. At a certain point, half of the participants move to the center, where they tap their right foot and return to their respective places. Then, the circle starts to rotate again, alternating the participants who go to the center (23, 24).

Vira was selected because it combines whole-body movements requiring balance, flexibility, endurance, upper extremity function, perceptual-cognitive skills, and memory. Using Vira’s short routine will allow participants to repeat the dance steps requiring mobilization of attention and memory. In addition, the steps are simple, easy to learn and promote the transfer of weight from one side to the other.

Participants will be taught how to execute movements safely, focusing on maintaining proper alignment, balance, and coordination. Movements will be introduced gradually, allowing participants to build strength, flexibility, and control over time. Due to safety concerns, the dance program will incorporate modifications and adaptations to accommodate individual needs and limitations. Participants will not dance in pairs in this protocol. The instructor will pair participants with poor standing balance with the assistants. The assistants will support the patient by holding hands to increase stability. In addition, participants with poor standing balance will be provided with a gait belt to allow assistants to help them if necessary. We will modify the training for participants with severely reduced balance by dancing in a wheelchair. The instructor will encourage these participants to move their arms and legs, move the wheelchair forward and backward, and perform flexion/extension or lateral flexion of the trunk. The program will take place in a spacious, well-maintained environment with shock-absorbent and non-slip flooring.

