Sessions will be led by a nurse specialized in rehabilitation expert in motor and cognitive exercise programs, and a background as a Portuguese folk dance instructor. We will consider eight stroke survivors as the optimum number of participants per session. Assistance to the instructor will be provided by three nurses that are receiving their master’s training in rehabilitation nursing, using a ratio of two participants for one therapist. In addition, the students will receive training to modify the exercises for each participant when needed and ensure their safety.

To provide a suitable level of challenge, the instructor will progressively increase the difficulty of the workouts accordingly to the participants’ willingness and improved condition. During sessions, the instructor will ask participants about their perceived effort through the Borg Effort Perception Scale (30). All professionals supervising the program application will provide the training’s adaptation, specificity, progression, variation, and safety. The structure of the training sessions is described in detail in Table 1.

**Table 1 tab1:** Structure of the training sessions.

Phase 1: Arrival (10 min)	Social interaction (e.g., greeting friends). A brief discussion on safety issues and how to participate (first-timers). Assess new health and issues linked to the sessions (second-timers).
Phase 2: Warm-up (10 min)	Group warm-up using whole-body amplitude movements incorporating neck, shoulders, hands, trunk, hips and knees movements, and slow passive stretching of the most affected upper extremity using the least affected upper extremity. Essential dance step (e.g., step touch) to increase heart rate. Walking in place or in chair, in a rhythmic routine using music based on group preferences. Voice warm up exercises with loud ahh, glides, and humming exercises.
Phase 3: Technical exercises (Two exercises per session; 10 min)	Trunk rotation. Step-touch side-ways. Moving the hips (side-ways). Weight shifting. Step-touch forward-backward. Basic step of the meringue. Sliding to the side. Twist.
Phase 4: Directed improvisation (10 min)	Participants will move freely according to some directions (bilateral movements only, large and big movements, etc.). In turn, they must either guide and be followed or follow the sequence proposed by another participant.

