Since this pilot study aims to determine the program’s acceptability and feasibility, our results will not allow us to determine that the participants’ health outcomes are due to the dance intervention. However, this study precedes the development of a randomized controlled trial that may prove the efficacy of adapted Portuguese folk dance as a therapeutic intervention for patients with stroke. If proven effective, the results should benefit stroke survivors by safely improving their balance and gait patterns. Additional benefits over clinical disease management, cognition, physical capacity, depression, and fear of falling are also expected. This will ultimately promote Portuguese folk dance as a rehabilitation intervention for stroke survivors, opening the door to testing its effectiveness, and acceptability in other populations in worldwide healthcare systems.

Although dance can be enjoyable, it can also be intimidating for people who have not previously participated in dance classes (47). However, incorporating Portuguese folk dance, part of the population’s cultural roots, in rehabilitation training can increase Portuguese stroke survivors’ adherence. In addition, this intervention has the potential to promote social interaction, as it will be performed in a group format. Therefore, we expect the participants to develop a sense of camaraderie (13, 14, 48) and accomplishment (14), contributing to the intervention’s satisfaction (13, 14). Given all these aspects, we believe incorporating Portuguese folk dance in rehabilitation training should be an especially well-adapted and attractive way of optimizing patient recovery after stroke.

As in previous studies that use dance intervention for stroke survivors in rehabilitation hospital settings, we expect the level of risks associated with the intervention to be low (14). However, the potential risks of a dance intervention should be anticipated and addressed to guarantee participants’ safety. Therefore, the instructor can adapt the exercise program and choreography to keep each participant’s skills and abilities challenging and engaging. In addition, as a safeguard, we will consider eight stroke survivors as the ideal number of participants for each session, depending on the stroke survivors’ dependence, thus achieving a ratio of two participants for one therapist.

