This study is not without limitations. First, the protocol will not include a control group, which will prevent comparing the effect of the dance intervention to additional treatment. Second, since stroke survivors are recruited in the subacute phase, some participants may suffer disease complications that stop them from attending the program.

Third, when assessing the program feasibility, we acknowledge the possibility of social desirability bias, as participants might report perceptions and feelings that might diverge from their emotions. Therefore, to minimize social desirability during the qualitative assessment, we will implement practices recommended by Bergen and Labonté (49). The interviews will be performed in a private location and not within earshot of others. The interviewer will use various approaches to establish rapport with participants, including humor, self-disclosure, and/or making displays of respect. We will clearly explain details about the study to participants, including how the data will be used and confidentiality and anonymity procedures. Suppose the interviewer suspects a response reflects social desirability tendencies. In that case, he will maintain a nonconfrontational and respectful posture and try to elicit a more accurate response by providing context when asking questions, acknowledging that people have diverse experiences, posing indirect questions, and requesting that participants provide a story or example to illustrate their response.

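### The safety outcome is defined in two conflicting ways: number and type of adverse events in the Abstract, but only events involving injury in Data collection

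*Protocol article*

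**What the plan says.** The protocol article states the safety outcome twice.

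- Abstract: "Safety will be assessed based on the number and type of adverse events". There is no restriction to injury, and the type of event is part of the outcome.
- Section 2.5 (Data collection): "Safety via adverse events (number of events involving injury". The words in parentheses restrict the count to injuries, and type is gone.

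Other parts of the article bear on how the outcome will behave:

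- Section 2.4 (Intervention) foresees balance problems during sessions: "participants with poor standing balance will be provided with a gait belt to allow assistants to help them if necessary". Those with severely reduced balance dance in a wheelchair.
- Table 1 (section 2.4), arrival phase, has an instruction to "Assess new health and issues linked to the sessions (second-timers". It is not linked to the safety outcome.
- The limitations in section 3 (Discussion) expect that "some participants may suffer disease complications that stop them from attending the program".
- The Discussion also says that "the potential risks of a dance intervention should be anticipated and addressed to guarantee participants’ safety".

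Section 2.6.1 (Quantitative evaluation) does not mention safety, so it does not resolve the difference.

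**The concern.** The two statements would give different safety results from the same events. Staff who follow section 2.5 would count injuries; a reader of the Abstract would expect every adverse event, sorted by type.

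The difference matters in this population. A participant with poor standing balance who starts to fall and is held by an assistant is an example of the gait belt doing its job, but adds nothing to an injury count. The same holds for a fall to the floor without harm, or for a cardiac or neurological event without injury. A disease complication that ends participation would appear as reduced retention and not as a safety event.

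Safety is a named outcome of a pilot that is meant to precede a randomised trial. If only injuries are counted, the trial's planners would receive a safety summary that leaves out foreseeable kinds of event. Unharmed falls that are not logged when they happen are hard to recover afterwards.

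**Working it through.** **1. The two definitions compared**

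| | Abstract | Section 2.5 |
|---|---|---|
| Events counted | all adverse events | only those involving injury |
| Type of event | yes | not mentioned |
| Fall without injury | may count | does not count |
| Medical event without injury | counts | does not count |

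No other section gives a wider definition or says which of the two governs.

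**2. Direction**

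Let A be the number of all adverse events and I the number involving injury. The events in I are a subset of those in A, so I ≤ A always. The shortfall A − I is the number of events without injury. If a share s of events involves injury, a fraction 1 − s is left out. The direction needs no assumption; the size depends on s, which the article does not give.

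**3. Illustration of size**

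The article states no safety figure to reproduce. Inputs:

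- n = 16 recruited (section 2.3). Applying the stated 25% dropout gives 16 × 0.75 = 12 completers; the 12 is inferred, not stated.
- p, the proportion of participants with an adverse event: assumed 20% to 30%.
- s, the share of events involving injury: assumed 10% to 50%.
- At most one event per participant, and independence between participants: assumed.

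Probability of a zero count:

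- all events: (1 − p)^n
- injury only: (1 − p·s)^n

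For n = 16:

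- All events: 0.80^16 = 2.8%; 0.70^16 = 0.3%.
- Injury only, p = 20%, s = 10%: 0.98^16 = 72%.
- Injury only, p = 30%, s = 50%: 0.85^16 = 7%.

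For n = 12 the ranges are 1.4% to 6.9% for all events and 14% to 79% for injury only. Because those who drop out are at risk until they leave, 16 is the more natural number.

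Over the assumed range of s, between 1 − 0.50 = 50% and 1 − 0.10 = 90% of events would fall outside the count.

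**4. What a zero count would show**

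With no events in n participants, the one-sided 95% upper limit is 1 − 0.05^(1/n): 17% for n = 16 and 22% for n = 12. The limit comes from the sample size and is the same number under either definition, so it does not measure the conflict. What changes is the quantity it bounds: under section 2.5 it limits the risk of an injurious event only.

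**5. Exposure**

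The programme has 8 weeks × 3 sessions = 24 sessions, so at most 16 × 24 = 384 participant-sessions. Section 2.5 already collects the number of classes attended, so the actual exposure can be computed.

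**The case against.** The strongest reply is that this is a difference of wording in a condensed article. Section 2.5 gives a one-line fragment, the Abstract gives the broader definition, and the full protocol may define adverse events properly. The primary aim is acceptability and feasibility, and no stopping rule, sample size or progression criterion in the text depends on the injury count. Complications that stop attendance would also be visible in retention, and health problems are asked about on arrival.

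Much of this is fair, and it limits the point. It does not remove it: two statements in the text conflict, and the more specific one is the narrower. Retention shows that someone stopped coming, without making the reason a safety event, and the arrival check feeds no defined outcome.

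Several stronger readings are tempting but not supported:

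- A reader might infer that events without injury will go unrecorded or be entered as zero. The article does not say so. They may appear in clinical records, the arrival check or attendance data; they are only outside the safety outcome as section 2.5 defines it.
- A reader might take "the results should benefit stroke survivors by safely improving their balance and gait patterns" as a safety conclusion that the pilot will draw. In the Discussion it is conditional on efficacy being proven, and follows the sentence on a later randomised trial.
- A reader might object that there is no exposure denominator. Classes attended supply one.
- A reader might fault the lack of seriousness grading, relatedness or confidence intervals. An article may leave these to the full protocol or the analysis plan.

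**Conclusion.** The point holds as an internal conflict. The Abstract and section 2.5 define safety differently, and section 2.5 is narrower in two ways: injury only, and number without type. If section 2.5 is followed as written, falls and medical events without injury do not enter the safety outcome, although the article itself makes them foreseeable. The safety result can then only equal or understate the count of all events.

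That direction is certain. The size is not known: the probabilities of a zero count (7–72% for injury only against 0.3–2.8% for all events, n = 16) rest wholly on assumed event rates and injury shares, and show only that the choice of definition can change the picture substantially. The documents do not support a claim that events will be lost, or that the pilot is set to declare the programme safe. The conflict should be resolved before the first session because it determines what is logged.

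**What to change.** Before the first session, reword the safety line in section 2.5 to agree with the Abstract: safety is the number and type of all adverse events during the programme, whether or not they involve injury, with falls without injury named explicitly. Report events involving injury as a subset, so the narrower count is still available.

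The instructor and assistants already present at each session can log the events, and the arrival check in Table 1 can feed the same log. Report the number of participants affected and the events per class attended, using the attendance data already planned.

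The cost is a short event log and a reported event count that will probably be higher than the injury count alone. Treatment, sample size and the assessment schedule are unchanged.

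### Satisfaction is surveyed after the program with no contact tied to withdrawal, so with the 25% dropout allowed for, the satisfaction result is at risk of upward bias

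*Protocol article*

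**What the plan says.** The Abstract sets out the acceptability aim: "Acceptability will be assessed by four key domains (enrollment, retention, satisfaction, and recommendation to others". Section 2.5 (Data collection) names the instruments for one of these domains: "satisfaction (assessed with a survey and semi-structured exit interviews". It places the survey after the intervention: the study coordinator "will administer a customized post-intervention survey to assess" how acceptable participants found the program. The same section gives the interviews the task of finding preferences, barriers and facilitators that bear on participation, and says the domains were chosen with a later randomized trial in mind.

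On losses, section 2.3 (Sampling and recruitment) states: "We aim to recruit 16 participants taking into account a dropout rate of 25" percent. The limitations in the Discussion add that "some participants may suffer disease complications that stop them from attending the program". They also describe detailed steps against social desirability bias in the interviews. They do not connect non-attendance with missing satisfaction data.

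Retention, a separate domain in section 2.5, is defined by classes attended and by the share of enrolled participants who complete the final assessments.

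**The concern.** A survey given after the program, and an interview at exit, reach most easily the people who are still there. The plan itself allows for a quarter of participants not being there. People who stop attending are the most direct source on what stood in the way of taking part, which is what the interviews are meant to find out. If they are not approached, the satisfaction figure describes people who stayed, and staying is itself related to finding the program acceptable.

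Two things are at stake. The satisfaction result may look better than it would among everyone enrolled. The barriers passed on to the randomized trial may be those of completers, who overcame them, and not those of leavers, who did not. Eligibility already requires a liking for the dance style, so losing dissatisfied leavers would add a second filter in the same direction. Neither loss can be repaired afterwards, because the views of leavers cannot be reconstructed from attendance records.

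**Working it through.** **Inputs**
- Recruitment target N = 16 and dropout allowance 25% (section 2.3).
- Satisfaction instruments: post-intervention survey and exit interview (section 2.5).
- Assumption: the 25% allowance is realized and none of the leavers is surveyed. The document does not state the second part; it is what the stated timing would probably produce.
- Assumption: satisfaction is summarized as a proportion satisfied. The document specifies Likert questions and gives no cut-off, so the counts below are illustrations.

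**Reproducing the plan's figure**
- Completers: 16 × (1 − 0.25) = 12. Leavers: 16 − 12 = 4.
- Inflating back: 12 / (1 − 0.25) = 16, which matches the stated target. The 12 is implied and not stated, so this shows consistency and does not derive the sample size.

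**Bounds on the satisfaction result**

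Let s be the number satisfied among 12 completers and d the number satisfied among 4 leavers (0 to 4).
- Reported figure: s/12.
- All-enrolled figure: (s + d)/16.
- Overstatement: s/12 − (s + d)/16 = (4s − 3s − 3d)/48 = (s − 3d)/48.

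| Satisfied completers | Reported | All enrolled, d = 0 | All enrolled, d = 4 | Overstatement, d = 0 | Overstatement, d = 4 |
|---|---|---|---|---|---|
| 12 of 12 | 100% | 12/16 = 75.0% | 16/16 = 100% | +25.0 points | 0 |
| 11 of 12 | 91.7% | 11/16 = 68.8% | 15/16 = 93.8% | +22.9 points | −2.1 points |
| 10 of 12 | 83.3% | 10/16 = 62.5% | 14/16 = 87.5% | +20.8 points | −4.2 points |

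**Reading the bounds**
- The overstatement is zero when d = s/3, that is, when leavers are satisfied in the same proportion as completers (d/4 = s/12). It is positive whenever leavers are less satisfied, and negative only when they are more satisfied.
- The range is lopsided when most completers are satisfied: up to 25 points too high, against about 4 points too low in these examples.
- The size scales with actual dropout. If all completers are satisfied and k people leave, the maximum overstatement is k/16. For k = 2 it is 2/16 = 12.5 points; for k = 4 it is 4/16 = 25 points.

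**The case against.** The strongest reply is that the article does not exclude anyone. Neither instrument is restricted to completers, and an exit interview can be held whenever a participant exits. The timing in the week after completion (T1) is stated for the balance and mobility measures, not for the survey or interviews. Procedures at withdrawal are also the sort of detail that an article may leave to a full protocol. This part stands: a reader might infer that leavers are left out, and the text does not say so. It neither excludes them nor provides for them. What remains is that the timing that is stated, post-intervention, is a poor choice for a domain of the primary aim when a quarter may leave, and that a better timing is available at little cost.

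A reader might also infer that the acceptability result as a whole is biased upward. The document does not support that. Retention is its own domain with all enrolled as denominator, so leavers lower it, and a reader would see it beside satisfaction. Retention does not, however, show why people left, and it does not correct a satisfaction percentage.

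A third tempting inference is that leavers are those who found the program least acceptable. The only cause of non-attendance that the protocol names is disease complications, which need not reflect dissatisfaction. The direction is therefore likely and not established, and without recorded reasons the study could not tell the two kinds of leaver apart.

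Finally, each session ends with a short group discussion, so future leavers are heard while they attend. That discussion is there to guide later sessions, is not named as a satisfaction measure, and does not reach people once they have stopped.

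**Conclusion.** The point holds for the satisfaction domain and for the barriers drawn from the interviews. Followed as written, both would probably rest on about 12 of 16 enrolled participants and are at risk of upward bias that the limitations do not mention. If all 12 completers were satisfied, the reported 100% could correspond to anything from 75% to 100% among all enrolled, an overstatement of 0 to 25 points.

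This rests on the full 25% dropout occurring, on leavers not being surveyed, and on satisfaction being reported as a proportion. With fewer leavers the range narrows in proportion. The point does not depend on any error in the sample size or in the paired analysis of balance and mobility.

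**What to change.** State in section 2.5 that the same survey and a short interview are offered at T1 or at withdrawal, whichever comes first, to every enrolled participant who is willing and able. Record the reason for leaving where the participant gives one. Report satisfaction with the number of responders out of the number enrolled, and add a worst-case line that counts non-responders as not satisfied.

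The wording about willing and able participants matters, because consent may be withdrawn at any time and illness may prevent contact; full coverage cannot be promised, and the worst-case line shows what remains unknown.

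The cost is about four extra brief contacts by the coordinator and interviewer already assigned. The setting is a rehabilitation center for people who cannot yet return home, so those who stop attending but remain there should be reachable. The downside is a possibly lower satisfaction figure.
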